#### Exclusion criteria

2.4.2

Participants will be excluded if they meet one of the following criteria: (1) With serious diseases, such as heart, lung, liver, and kidney failure; (2) With other neurological conditions that cause motor deficits, such as Parkinson’s disease, multiple sclerosis, and peripheral neuropathy; (3) Epileptic seizures; (4) With cognitive impairments, Mini-Mental State Examination (MMSE) ≤24 scores, unable to cooperate with researchers to finish the interventions or assessments; (5) With severe aphasia and communication difficulties that may influence the intervention and outcome measures; (6) With severe pain, Visual Analog Scale (VAS) ≥7 scores; (7) With moderate or severe depression, anxiety and other psychological disorders; (8) With contagious conditions or diseases, particularly of eyes, skin, scalp, or forearm; (9) With implanted medical devices or materials, such as pacemaker and metal implants; (10) With contraindications for NMES, such as skin injuries or skin diseases, acute infections, vascular diseases in the affected forearm; (11) With other diseases limiting upper extremity and hand functions, such as fracture, joint injury, and muscle pain of the affected arm; (12) With vestibular diseases, digestive problems that limit the use of VR headset; (13) Surgery and other invasive treatments; (14) Participants with a recurrent stroke or any medical condition that may affect safety or accuracy of evaluation results will also be excluded (29).

In addition, we will use structural MRI to calculate lesion volumes, including hemorrhage size (for hemorrhagic strokes) and infarct volume (for ischemic strokes). Automated or semi-automated segmentation tools (e.g., MRIcron, ITK-SNAP) will be applied to ensure accuracy and reproducibility (30). Lesion locations will be mapped to standardized brain atlases [e.g., Montreal Neurological Institute (MNI) space] using voxel-based or region-of-interest approaches. This will allow precise documentation of cortical/subcortical involvement (e.g., motor cortex, corticospinal tract, parietal regions) (31). Participants will be stratified into subgroups based on stroke type, lesion volume and location. What’s more, we will meticulously record the time elapsed from stroke onset to the initiation of rehabilitation, including the start of conventional rehabilitation therapy and AOT.

### Randomization and blinding

2.5

Through a computerized block randomization protocol, the participants meeting the eligibility criteria will be randomly assigned to control group or experiment group. The random allocation sequence will be generated by the R package blockrand version 1.5, with randomly ordered blocks of size 6 or 8, and a 1:1 allocation ratio. The randomization cards generated by the blockrand version 1.5 package will be printed out and enclosed in sequentially numbered, opaque, sealed, and stapled envelopes. The allocation sequence will be concealed from the researcher responsible for enrolling and evaluating participants. Corresponding envelopes will be opened only after the enrolled participants have completed all the baseline assessments and at the time of allocation to the intervention. An independent study coordinator who will not oversee assessments and interventions will design and conduct the randomization sequence generation and group allocation. Only the study coordinator and principal investigator (PI) have access to group assignment materials locked in a binder.

Due to the nature of rehabilitative interventions, it is impossible to blind participants, their caregivers, and therapists participating in the treatment. In this study, the assessor and data analyst will be blinded throughout the trial. The participants will be instructed not to disclose their allocation to investigators or outcome assessors. The therapists who conduct the treatment will be asked not to disclose the participant’s group assignment during the whole study period (12). In addition, they will not evaluate the participants and have access to the evaluation results (29). To mitigate the potential performance bias due to the lack of participant/therapist blinding, we will take the following actions. Firstly, we will make standard operating procedures (SOPs) for all the assessments and interventions. Adhering to the SOPs will ensure consistency in how the assessments and interventions will be administered across all participants, reducing variability introduced by therapist behavior. Secondly, all the therapists will be trained thoroughly on the SOPs, their adherence throughout the trial will be monitored. Thirdly, we will ensure that the informed consent process does not inadvertently reveal the hypothesized advantages of the experimental intervention. Fourthly, we will actively monitor for signs of performance bias during the trial, such as differential dropout rates or adherence patterns between groups. If participants inadvertently or intentionally reveal treatment details to assessors, we will record all unblinding incidents (timing, cause, and impact) and report them in study publications per CONSORT guidelines.

### Intervention

2.6

The experiment group will receive VRAO+NMES, while the control group will receive VR landscape observation (VRLO) + NMES; both groups will receive conventional comprehensive rehabilitation therapies and routine medical treatments. During the intervention, the participant will sit upright in a relaxed way, wearing the VR headset and attaching the NMES electrodes. All the intervention sessions will be supervised by certified physiotherapists with more than 5 years of experience. For both groups, the intervention period will last 4 weeks, with a frequency of 5 times a week, and 20 min per session.

To implement the interventions and assessments, we designed a specific VR-based integrated rehabilitation evaluation and training system. The system manages the presentation of VR visual stimulation and the triggers to control the ES output (32). The experiment program adopts block design, the task duration is 15 s and rest duration is 20 s in each block, the electrical output is on during the task period and off during the rest period; this protocol has been confirmed by our previous study (21). Except for contents of the videos, action videos for the experiment group and landscape videos for the control group, all the other parameters are same in both groups. The first-person and third-person point of view 360° VR video clips of actions and landscapes will be shot using an Insta360 one X2 camera, and edited by Insta360 studio v5.2.4 (Insta360 Inc., Shenzhen, China). The videos and experiment cues will be presented through a Oculus Quest 2 VR headset (Meta Platform Inc., CA).

At the beginning of the study, the therapist will explain treatment process to the patient in advance. During each intervention session, the patient will sit in an upright and relaxed position, the therapist will determine the motor points of the target muscles. After disinfecting the skin with medical alcohol, the therapist will stick electrodes and fix cables according to the determined motor points. After putting the VR headset on the participant’s head, the experiment program will be turned on, at this time, the participant could see the visual stimulations and feel the electrical stimulations. A laptop will be linked to the VR headset to display the contents seen by the participant, allowing the therapist to monitor the interventions. During the treatment, the therapist will always be present, observing the patient’s reaction and making treatment records. The participant will be told to stop the intervention at any time if they feel discomfort.

#### Experiment group

2.6.1

In the experiment group, 360° VR action videos will be played during the NMES output period. During task phase, participants will be guided to view the VR action videos and feel the NMES induced hand movements. During rest phase, they will be encouraged to try their best to imagine or imitate the observed actions. We will build a database of 360° action videos performed by different models with different age ranges, genders, and heights. For each participant, we will choose the most similar model’s action videos according to the participant’s demographic and clinical information, mainly the affected/impaired side, gender, and age. Basic actions of single joints, goal directed actions, and daily life actions will be recorded, including unimanual and bimanual actions. In each treatment session, 4 basic actions and 12 daily life actions will be selected according to the participant’s motor ability. The actions observed in each session will be arranged according to their difficulty and complexity. For each round, a single joint basic movement’s 360° video, such as wrist extension, will be observed first, followed by three daily life actions’ 360° videos, such as picking up objects from the desktop, typing, and holding a pen.

In this study, a customized made electrical stimulation device will be made to conduct the personal treatment protocol: waveform: rectangular; phase duration: 200 μs; pulse frequency: 50 Hz; burst frequency: 1 Hz; ramp up time: 1 s; hold time: 15 s; ramp down time: 1 s; interval time: 18 s. This NMES treatment protocol has been validated by our previous studies (11, 21). The electrical intensity for each patient will be individualized to minimize evoked muscle contractions and avoid discomfort (11).

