Due to the effects of action visual stimulation on MNS and ES on motor units (MUs), VRAO+NMES may be helpful to accelerate the process of motor learning. In addition, the enhanced multisensory interactions generated by VRAO+NMES have potential to improve the alteration of body ownership and induce self-body recognition (23). To investigate the potential neuromuscular control mechanism underlying this new intervention, we will use functional near-infrared spectroscopy (fNIRS) and surface electromyography (sEMG) to evaluate the activation of brain regions and muscles, respectively. In addition, MNS network-based neuroplasticity changes have been confirmed recently, we will also explore the brain functional connection changes before and after the interventions (25).

We, therefore, aim to determine whether a concurrent application of VRAO and NMES would result in significant improvements in behavioral assessments and neurophysiological parameters, and to test whether the changes in motor function evaluated by clinical scales are related to the brain functional imaging results measured by fNIRS. We hypothesize that VRAO+NMES is superior in improving upper extremity and hand motor functions, ADLs, and MNS cortical activation levels compared to conventional therapy plus NMES. The underlying mechanism may be that the brain-muscle synchronous intervention enhances activation of the MNS and recruitment of MUs, thereby promoting brain plasticity changes, improving neuromuscular control function, and enhancing therapeutic effects.

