### Safety and AE reporting

2.13

All the safety related events occurring during the study period will be monitored and recorded by the therapists. In addition, AEs and SAEs will be reported to the Medical Ethics Committee of CRRC and relevant scientific research management and regulation institutions, they will be categorized as related/not related and expected/not expected.

To ensure patient safety, before each session, the therapist will confirm with the participant and their caregivers that none of the following problems existed: bad sleep, alcohol or drugs use, emotional stress or anxiety, cold, flu, headaches, and migraines. During the interventions or evaluations, the therapist will monitor and record the following potential side effects and discomfort caused by VR or ES: seizures; dizziness; nausea; lightheadedness; motion sickness; loss of awareness; eye strain or muscle twitching; blackouts triggered by light flashes or patterns; involuntary movements; altered, blurred, double vision, or other visual abnormalities; disorientation; excessive sweating; increased salivation; and tiredness or exhaustion.

The intervention or assessment will be immediately discontinued if any of the above symptoms is experienced. After each session of intervention and evaluation, the therapist will survey if the following possible side effects or discomforts occur: visual disturbance; visual and muscular fatigue; upper extremity or neck pain, or musculoskeletal discomfort; VR motion sickness; claustrophobia; cybersickness; nausea; soreness; dizziness; headache; and hypertonicity (45).

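### The NMES intensity target and the trigger for stopping a session are not coherently stated (Sections 2.6.1 and 2.13)

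*Protocol article*

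**What the plan says.** **Intended effect.** In the task phase, Section 2.6.1 of the protocol article states that "participants will be guided to view the VR action videos and feel the NMES induced hand movements". The Introduction gives the hypothesised mechanism as follows: "the brain-muscle synchronous intervention enhances activation of the MNS and recruitment of MUs". Section 2.6 has the therapist locate motor points and place the electrodes accordingly.

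**Intensity.** Later in Section 2.6.1: "The electrical intensity for each patient will be individualized to minimize evoked muscle contractions and avoid discomfort". The article gives no threshold or visible-response criterion.

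**Stopping.** Section 2.13 introduces a list of possible side effects and discomfort from VR or electrical stimulation. It includes "eye strain or muscle twitching; blackouts triggered by light flashes or patterns; involuntary movements". The rule that follows is mandatory: "The intervention or assessment will be immediately discontinued if any of the above symptoms is experienced".

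**Timing.** Section 2.6 says "the task duration is 15 s and rest duration is 20 s in each block" and that "the electrical output is on during the task period and off during the rest period". Section 2.6.1 gives the device settings as "ramp up time: 1 s; hold time: 15 s; ramp down time: 1 s; interval time: 18 s".

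**Common to both arms.** Section 2.6 states that only the video content differs between the groups.

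**The concern.** A hand movement induced by NMES requires an evoked contraction. One sentence of Section 2.6.1 relies on that movement; another asks for contractions to be minimised. A therapist working to the first would look for a movement the participant can feel, and one working to the second would aim for as little as possible.

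The stop rule adds to this. In plain words, a movement produced by NMES is an involuntary movement caused by electrical stimulation. Section 2.13 has no wording that excludes it, and the rule also covers assessments. The fNIRS task runs in Section 2.7.3 deliver NMES, so they fall under it too.

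The stakes are fidelity and reporting. Section 2.5 says therapists cannot be blinded and relies on standard operating procedures to limit performance bias. Procedures cannot be consistent if their source text conflicts. One therapist could record an expected contraction as a side effect and stop, while another carries on and records nothing. The instruction to feel induced movements also stands only under the experiment group (2.6.1) and not under the control group (2.6.2), so the conflict could be resolved differently by arm.

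**Working it through.** **1. Intensity: statements side by side (no arithmetic applies)**

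| Place | Statement in brief | Implication for evoked contraction |
|---|---|---|
| Introduction | Motor unit recruitment is part of the mechanism | Some motor response expected |
| 2.6 | Electrodes placed by motor points | Some motor response expected |
| 2.6.1, task phase | Participant feels induced hand movement | Must be enough to move the hand |
| 2.6.1, device paragraph | Intensity set to minimise evoked contraction | As little as possible |

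The last two rows pull in opposite directions. They can be reconciled if minimising means the smallest contraction that still moves the hand, but the article does not say so.

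**2. Stop trigger**

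- Expected response (2.6.1): hand movement caused by NMES.
- Listed symptoms (2.13): muscle twitching and involuntary movements, from VR or electrical stimulation.
- Consequence (2.13): immediate discontinuation for any listed symptom.
- Exclusion of the expected response: none stated.

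On a literal reading, the trigger is met in any session where NMES moves the hand. On a reading governed by the list's introduction (side effects and discomfort), it is not met. The text permits both.

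**3. Timing (minor)**

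Inputs: 15 s task and 20 s rest (2.6); ramp up 1 s, hold 15 s, ramp down 1 s, interval 18 s (2.6.1).

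- Cycle by block design: 15 + 20 = 35 s.
- Cycle by device settings: 1 + 15 + 1 + 18 = 35 s. The cycles agree.
- Hold only counted as on: 15 s on, and 1 + 1 + 18 = 20 s otherwise. This reproduces 15/20 exactly.
- Any output counted as on: 1 + 15 + 1 = 17 s on, 18 s off. This does not reproduce 15/20.
- Share of the cycle: 15/35 = 42.9% against 17/35 = 48.6%.

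Assuming back-to-back blocks (not stated), a 20-minute session holds 1200/35 = 34.3 blocks. The difference is 34.3 × 2 s ≈ 69 s of ramping per session: 34.3 × 17/60 = 9.7 min against 34.3 × 15/60 = 8.6 min of output.

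Because 17 s of output cannot fit inside a 15 s task, 2 s falls in the rest period whatever the alignment, at partial amplitude if the hold coincides with the task.

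**4. Does the ramp matter for fNIRS?**

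A 15 s on/off regressor was compared with a 1 + 15 + 1 s ramped input. Assumptions: a standard double-gamma haemodynamic response, 8 cycles of 35 s as in Section 2.7.3, and ramp onset 0 to 2 s before the task. The regressors correlated at about 0.98 to 0.997, with slopes of 0.99 to 1.01. The effect is negligible. Both fNIRS conditions also include NMES, so the ramps are common to their contrast.

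**The case against.** **Intensity.** Minimising is not abolishing. A small evoked movement can still be felt, intensity is individualised, and the sentence may be a slip for minimal contractions. Titration detail can properly sit in the operating procedures, which a condensed article would not reproduce. This makes an innocent reading available, but the finding is not that detail is missing. Two sentences in the article conflict as written, and nothing in it settles them.

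**Stop list.** The list is introduced as side effects and discomfort, and its other items, such as seizures and loss of awareness, are warning signs. Intended responses were probably not meant, and sessions are supervised by experienced, trained physiotherapists. That stands as the likelier intention. It does not remove a mandatory rule whose wording covers the expected effect.

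**Stronger readings the documents do not support.** A reader might infer that the delivered treatment is undefined. It is not: waveform, phase duration, pulse and burst frequency, ramps, hold, interval, session length and the 20 sessions are all fixed. A reader might infer that the arms will differ in NMES and the comparison is biased. Section 2.6 makes all settings other than the videos the same, so differential delivery is a possibility and is not shown. A reader might infer from the 17/18 split that on-time is materially wrong or that the fNIRS baseline is materially contaminated. The 15 s hold equals the 15 s task, and the check above shows a negligible effect, so the regressor need not change. Adverse event counts become harder to interpret, not uninterpretable.

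**Conclusion.** The concern holds for two items: the intensity target, and whether expected evoked movement is a reason to stop. These are conflicts between stated rules; followed literally, they would undercut or halt the treatment under test. The consequence is weaker fidelity and reproducibility, and less interpretable counts of stopped sessions and side effects. No number can be put on it, since the article gives no intensity, response or stopping data. Any effect on the between-arm comparison would require therapists to resolve the conflict differently by arm, which is plausible because they are unblinded but does not follow from the text.

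The timing discrepancy is minor: two 1 s ramps per 35 s cycle, an unstated convention. Nothing here bears on the sample size, alpha or power. The point should be corrected, but it does not undermine the design.

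**What to change.** The sponsor should reconcile Sections 2.6.1 and 2.13 promptly, with the clinical team deciding the content:

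1. Give one statement of the intensity target, consistent with what the participant is expected to feel.
2. Give one statement of whether the expected NMES-evoked movement is a listed symptom in Section 2.13, for both recording and discontinuation.
3. Apply both identically in the two arms and carry them into the operating procedures.
4. Log the intensity used and any stopped session, with its reason, in the existing treatment records, and summarise them by arm.
5. As a minor addition, state how the two 1 s ramps fit the 15 s on and 20 s off block of Section 2.6.

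The cost is a few sentences of protocol and SOP text and, if not already present, two fields on the treatment record. No change to the sample size, the outcomes or the fNIRS model is needed.

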#### Control group

2.6.2

As contrast, participants in the control group will watch VR landscape videos during the NMES outputs. The landscape VR videos will be shot by the research team, mainly of nature sceneries of gardens.

### Outcomes

2.7

All participants will be evaluated by clinical scales, fNIRS, and sEMG before and after 4 weeks of interventions. At baseline, sociodemographic and neurologic data will be collected, including age, gender, Body Mass Index, education, medical history, type of stroke, location of injury, and duration of disease. In addition, questionnaire surveys about safety, satisfaction, and feedback will be performed at the end of the interventions. Adverse events and serious adverse events will be monitored from the beginning to the end of the study. Expert therapists with above 10 years of experience will conduct the functional measures.

#### Primary outcome

2.7.1

The Fugl-Meyer Assessment for Upper Extremity (FMA-UE) is the primary outcome of this study, which is a 33-item scale used to assess motor function impairment in stroke survivors. Its reliability and validity have been well demonstrated (33). The minimal clinically important difference (MCID) score of FMA-UE is 4.25 scores (34). We hypothesize that more patients will reach a clinically relevant difference of 4.25 scores in the treatment group versus the control group.

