### Sample size

2.10

The primary outcome of this study is FMA-UE. A power analysis of the independent sample t-test was conducted using R package pwr version 1.3.0. According to a previous study, the effect size (d) was set at 0.8, the significance level was 0.05, and the power was 0.85; the calculated sample size was 60 participants in total, 30 participants in each group (43). Based on a dropout rate of 5%, it is estimated that 32 participants need to be recruited in each group.

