### Statistical analysis

2.12

For continuous variables, Shapiro–Wilk normality tests will be performed to assess their normality. Data following normal distribution will be expressed as mean ± standard deviation (SD), while the non-normal distributed data will be described as median and interquartile range (IQR). If each group’s data conforms to normal distribution and homogeneity of variance, the independent sample *t*-test will be used to compare the inter-group difference, and the paired *t*-test will be used to compare the intra-group difference pre- and post-interventions. If the data does not conform to normal distribution and homogeneity of variance, the non-parametric tests will be used for comparisons between and within groups. The categorical variables will be expressed as frequency and percentage; Chi-square test will be used for comparison between and within groups. Pearson or spearman correlation analysis will be used to test the correlation between variables according to their distributions. The significance level will be set as *α* = 0.05. We will use R version 4.2.3 and RStudio version 2024.04.21 (Posit Software, MA) to conduct the statistical analysis (44).

All the analyses will be conducted based on the Intention-To-Treat principle. For participants who quit the study midway, a subgroup analysis will be conducted with the collected outcome data. After the first 20 participants have finished all the evaluations, an interim analysis will be conducted according to the statistical analysis plan.

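### The hypothesis under the primary outcome compares responder proportions, but the stated 0.85 power is for a t-test on means and does not apply to it

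*Protocol article*

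**What the plan says.** Section 2.7.1 of the protocol article opens with "The Fugl-Meyer Assessment for Upper Extremity (FMA-UE) is the primary outcome of this study", gives 4.25 points as the minimal clinically important difference, and closes with "We hypothesize that more patients will reach a clinically relevant difference of 4.25 scores in the treatment group versus the control group". This is the only hypothesis under the primary outcome.

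Section 2.10 repeats that FMA-UE is primary and continues: "A power analysis of the independent sample t-test was conducted using R package pwr version 1.3.0". Its inputs are "the effect size (d) was set at 0.8, the significance level was 0.05, and the power was 0.85", giving 30 per group. It then adds: "Based on a dropout rate of 5%, it is estimated that 32 participants need to be recruited in each group".

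Section 2.12 assigns continuous variables to the independent-sample t-test, or a non-parametric test if assumptions fail. For categorical variables it says "Chi-square test will be used for comparison between and within groups". It does not link either test to the primary outcome.

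The Introduction has a more general statement: "We hypothesize that VRAO+NMES is superior in improving upper extremity and hand motor functions, ADLs, and MNS cortical activation levels". A comparison of means would fit that wording.

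**The concern.** A patient who gains at least 4.25 points is a responder, so the 2.7.1 sentence describes a binary endpoint. Under the general rules of 2.12, that comparison would go to a chi-square test. The only power calculation is for a different test on a different scale.

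Dichotomising a continuous score normally discards information. The responder comparison would then have less power than the t-test on the same data. The two analyses can also disagree. With about 60 patients, a significant mean difference beside a non-significant responder comparison, or the reverse, is quite possible. If the text is not reconciled, readers of the results cannot tell from this document which comparison was meant to answer the primary question.

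This is more than detail left for a statistical analysis plan. Sections 2.7.1 and 2.10 point to different comparisons, and a later plan that chose one would still leave the other section needing correction.

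**Working it through.** **1. The plan's own figure.** Inputs from 2.10: d = 0.8, alpha = 0.05, power = 0.85. Sidedness is not stated. With the noncentral t distribution, two-sided, n = 29.05 per arm, which rounds up to 30. Power is 0.849 at 29 per arm and 0.861 at 30. A one-sided test would need only 23.2, so the two-sided reading is the one that fits. Dropout: 30 / (1 − 0.05) = 31.6, so 32 per arm. The stated sample size is right for a t-test on means.

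**2. The same effect as a responder comparison.** The protocol gives no responder rates, so they must be assumed. Take normal change scores with equal SDs, and d = 0.8 on the change scale. If the control rate is p_c, the treatment rate is p_t = Φ(Φ⁻¹(p_c) + 0.8). Power is highest when 4.25 lies midway between the two arm means:

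- p_c = Φ(−0.4) = 0.345
- p_t = Φ(+0.4) = 0.655

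Exact power by enumerating both binomial distributions, 30 per arm, two-sided 0.05:

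| Control rate | Treatment rate | Uncorrected chi-square | Fisher or Yates |
|---|---|---|---|
| 10% | 31.5% | 0.550 | 0.424 |
| 20% | 48.3% | 0.645 | 0.546 |
| 34.5% | 65.5% | 0.694 | 0.594 |
| 50% | 78.8% | 0.651 | 0.552 |
| 70% | 90.7% | 0.538 | 0.405 |

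If all 32 recruited per arm are analysed, the most favourable row becomes 0.743 and 0.652.

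**3. Size needed for 0.85 power in the most favourable row.** Normal approximation: n = [1.960·√(2·0.5·0.5) + 1.036·√(0.345·0.655 + 0.655·0.345)]² / (0.655 − 0.345)². With unrounded rates this is 44.9, so 45 per arm, or 52 with continuity correction. After 5% dropout: 45 / 0.95 = 47.4, so 48; 52 / 0.95 = 54.7, so 55.

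**4. Sensitivity to what d = 0.8 refers to.** Section 2.10 does not say whether d is on change scores or week-4 scores. If it is on week-4 scores, with equal SDs and pre-post correlation r, the standardised effect on change is 0.8 / √(2(1 − r)). Exact power at the most favourable cut-off, 30 per arm:

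| r (assumed) | Effect on change | Uncorrected chi-square | Fisher or Yates |
|---|---|---|---|
| 0.3 | 0.676 | 0.55 | 0.45 |
| 0.5 | 0.800 | 0.69 | 0.59 |
| 0.6 | 0.894 | 0.79 | 0.70 |
| 0.7 | 1.033 | 0.89 | 0.83 |
| 0.8 | 1.265 | 0.97 | 0.95 |

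The figures in step 2 therefore equal the r = 0.5 case here. At r of about 0.7 to 0.8, the most favourable responder power reaches or passes 0.85.

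**The case against.** The strongest reply is that the document does favour a comparison of means. The Introduction's hypothesis is superiority in improving motor function. Section 2.10 moves directly from FMA-UE as primary outcome to the t-test, and 2.12 assigns that same test to continuous variables. The 4.25-point sentence follows the definition of the minimal clinically important difference and can be read as an expectation about clinical relevance. The chi-square sentence in 2.12 is generic and mentions neither FMA-UE nor 4.25.

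Much of this stands, and it rules out two stronger readings:

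- A reader might infer that the protocol declares two primary tests and can claim success on either. It does not. No section labels a responder endpoint or test as primary.
- A reader might infer that responder power is at most 0.59 to 0.69. The document does not support that bound. It needs d = 0.8 on change scores and exactly 30 analysed per arm. Section 2.10 recruits 32 per arm, 2.12 states intention-to-treat, and the scale of d is not given.

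The reply does not remove the mismatch. The responder sentence is still the only hypothesis under the primary outcome, and nothing in the sample-size section supports it.

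**Conclusion.** The point holds as an inconsistency between 2.7.1 and 2.10. It is not an arithmetic error: 30 per arm, inflated to 32, is correct for the t-test. The stated 0.85 power does not apply to the hypothesis as worded in 2.7.1, and the responder comparison has no sample-size basis because no rates are given.

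The size of the shortfall can only be illustrated. With d = 0.8 on normal change scores, equal SDs and a two-sided 0.05 test, the most favourable case has power of 0.59 to 0.69 at 30 per arm, or 0.65 to 0.74 at 32, and less at other cut-offs. If d = 0.8 is on week-4 scores and the pre-post correlation is high, there may be no shortfall.

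**What to change.** In 2.7.1 and 2.12, name the between-arm difference in mean FMA-UE at week 4 as the single primary analysis. Reword the 2.7.1 hypothesis as a difference in means, so that the 2.10 power statement applies to it.

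Preferably adjust for the baseline FMA-UE, which is already collected. This is not needed to resolve the mismatch, but it keeps the 2.10 calculation safe on either reading of d. With equal SDs σ, the adjusted residual variance is σ²(1 − r²). For r between 0 and 1, that is no larger than σ² (week-4 scores) or 2σ²(1 − r) (change scores).

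Make the proportion gaining at least 4.25 points a secondary supportive analysis, reported as a risk difference with 95% CI. State that the 0.85 power does not cover it.

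Cost: wording only, with no extra patients or assessments. The downside is that the responder claim becomes secondary. If the sponsor wants the responder comparison as primary, it must state the assumed rates and recalculate. On the illustration above, that means about 45 to 52 evaluable per arm (48 to 55 recruited) in the most favourable case.
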